### Summary:

This analysis is the third step (Aim 2) in a larger project to estimate the impact of enteric vaccines on etiology-specific diarrhea, antibiotic use, and exposure of subclinical infections to antibiotics among children in low-resource settings. Specifically, this analysis will estimate the impact of introducing two-dose series enteric vaccines with varying vaccine schedules (6&9, 9&12, 12&15 months), levels of indirect protection, effects on severity but not incidence, and vaccine efficacies. We will begin the analyses by focusing on hypothetical *Shigella* vaccines, with plans to analyze vaccines against additional enteric pathogens (e.g. *Campylobacter*, norovirus, enterotoxigenic *Escherichia coli* (ETEC), and rotavirus (vaccine available)). As in the previous analyses, we will analyze existing data from 1,715 children from the Malnutrition and Enteric Disease (MAL-ED) study.

Based on the different scenarios outlined above, will extend the results from Aim 1a (attributing diarrheal episodes that cause treatment) and from Aim 1b (attributing bystander antibiotic exposures for subclinical pathogens to diarrheal pathogens). Analyses will be performed at the level of diarrheal episode (N=6,677) from Aim 1a. We will then merge in the number of subclinical pathogen exposures to antibiotics per diarrheal episode from Aim 1b. We will use the attributable fractions per episode (AFe) for diarrheal pathogens that were calculated in Aim 1a where a pathogen with an AFe >0.5 is considered the cause of the diarrheal illness. We will then simulate how much antibiotic exposure calculated in Aims 1a (<https://osf.io/e4bqr/>) and 1b (<https://osf.io/3asxh/>) can be prevented with a vaccine. To simulate, we will perform Monte Carlo simulations with random sampling of the dataset with replacement to a sample size of 50,000. 95% confidence intervals for all parameters will be estimated by bootstrap with 1,000 resamples.

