### Analyses:

#### Probabilistically sample observed episodes as “prevented” by vaccine and re-calculate incidence

We will start with a vaccine for *Shigella* with dosing at 6 and 9 months of age. We will assume 60% efficacy 14-days after administration of the second dose. For simplicity, we will assume 0% efficacy prior to this time point. The Monte Carlo simulation will then be performed over the dataset with 50,000 samples under two scenarios: vaccine and no vaccine. For the vaccine scenario, we will probabilistically assign whether diarrheal episodes attributable to *Shigella* (defined by AFe > 0.5) would have been prevented assuming 60% efficacy. It is important to note that *Shigella* infections increase with age therefore, 60% efficacy will not directly translate to a 60% reduction in diarrheal illnesses. Additionally, there is low natural immunity (~20%) against subsequent *Shigella* diarrhea when considering all serotypes and species, so prior infection will not be factored in (Rogawski McQuade 2020 J Infect Dis),

at least initially. In a later iteration of the analyses, we may incorporate potential clustering of prevented episodes within children (i.e. all episodes among 60% of children are prevented, rather than 60% of episodes prevented overall, regardless of the child). We may also incorporate the potential for herd immunity among children too young to be vaccinated, partial efficacy after a single vaccine dose, different vaccine schedules (6&9, 9&12, 12&15 months), effects on severity in addition to or instead of incidence, and varying levels of vaccine efficacy. For the no vaccine scenario, no *Shigella*-attributable episodes would be prevented. We will conduct a sensitivity analysis where we define shigella diarrhea by any detection of shigella rather than AFe > 0.5.

We will estimate the expected reductions due to a *Shigella* vaccine in the following metrics:

1. Antibiotic treated severe *Shigella* diarrhea episodes

$$\left( \frac{N_{\text{antibiotic treated severe diarrhea episodes attributed to Shigella}} * \frac{\text{total number of diarrhea associated courses}}{\text{Total number of linked diarrhea associated courses}}}{\text{total child years of follow up}} \right) * 100$$

2. Antibiotic treated *Shigella* diarrhea episodes

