$$\left( \frac{N_{\text{antibiotic treated diarrhea episodes attributed to Shigella}} * \frac{\text{total number of diarrhea associated courses}}{\text{Total number of linked diarrhea associated courses}}}{\text{total child years of follow up}} \right) * 100$$

3. Antibiotic treated severe diarrhea episodes of any etiology

$$\left( \frac{N_{\text{reported severe antibiotic treated diarrhea episodes}} * \frac{\text{total number of diarrhea associated courses}}{\text{Total number of linked diarrhea associated courses}}}{\text{total child years of follow up}} \right) * 100$$

4. Antibiotic treated diarrhea episodes of any etiology

$$\left( \frac{N_{\text{reported antibiotic treated diarrhea episodes}} * \frac{\text{total number of diarrhea associated courses}}{\text{Total number of linked diarrhea associated courses}}}{\text{total child years of follow up}} \right) * 100$$

5. Antibiotic courses overall

$$\left( \frac{N_{\text{reported antibiotic courses}} * \frac{\text{total number of diarrhea associated courses}}{\text{Total number of linked diarrhea associated courses}}}{\text{total child years of follow up}} \right) * 100$$

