## 7. Antibiotic exposures to subclinical pathogens overall

$$\left( \frac{N \text{ times any bacterial pathogen exposed to antibiotic} * \frac{\text{total number of diarrhea associated courses}}{\text{Total number of linked diarrhea associated courses}}}{\text{Total number of linked courses}} \right) * \left( \frac{\text{Total number of courses}}{\text{Total child years of follow up}} \right) * 100$$

To estimate the expected reductions in #1-7 listed above, we will compare the relative and absolute differences between the vaccine and no vaccine simulations.

Relative difference, is expressed as a ratio of the metric between the vaccine simulations and the no vaccine simulation, which will be calculated as:

$$\frac{\text{vaccine simulation}}{\text{no vaccine simulation}}$$

Or the percent change as:

$$\frac{\text{vaccine simulation} - \text{no vaccine simulation}}{\text{no vaccine simulation}}$$

Absolute difference, which captures the true distance between two values, will be calculated as:

$$| \text{vaccine simulation} - \text{no vaccine simulation} |$$

As a secondary outcome, we will estimate the average age of *Shigella* diarrhea under the vaccine and no vaccine scenarios to determine whether the vaccine would be expected to increase the average age of disease.

Future directions:

Once we have the *Shigella* vaccine simulation running, we will compare the impact of a *Shigella* vaccine to that for other enteric vaccines, most importantly rotavirus. We may also include a comparison to a broad stewardship intervention that is not targeted to a specific pathogen.

Added Sept 12, 2022:

We will estimate the expected reductions in diarrheal episodes caused by *Shigella* and any etiology (regardless of whether the episode was treated):

1. Severe *Shigella* diarrhea episodes

$$\left( \frac{N_{\text{severe diarrhea episodes attributed to Shigella}} * \frac{\text{total number of diarrhea episodes}}{\text{Total number of diarrhea episodes validly tested by TAC}}}{\text{total child years of follow up}} \right) * 100$$

2. *Shigella* diarrhea episodes

$$\left( \frac{N_{\text{diarrhea episodes attributed to Shigella}} * \frac{\text{total number of diarrhea episodes}}{\text{Total number of diarrhea episodes validly tested by TAC}}}{\text{total child years of follow up}} \right) * 100$$

3. Severe diarrhea episodes of any etiology

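### Metrics 5 and 7 are overall totals, but the simulated file holds only diarrheal episodes, and formula 5 applies a diarrhea-only ratio to every course

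*Protocol*

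**What the plan says.** The Summary sets the unit of analysis: "Analyses will be performed at the level of diarrheal episode (N=6,677) from Aim 1a". Bystander data enter at the same level: "We will then merge in the number of subclinical pathogen exposures to antibiotics per diarrheal episode from Aim 1b". The simulation is then described as "random sampling of the dataset with replacement to a sample size of 50,000". In the Analyses section the vaccine scenario can remove only *Shigella*-attributed diarrheal episodes.

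The list of outcomes includes metric 5, "Antibiotic courses overall", and metric 7, "Antibiotic exposures to subclinical pathogens overall". Metric 5 is listed separately from metric 4 (treated diarrhea of any etiology). Formulas 6 and 7 use the total of all courses as a quantity distinct from diarrhea-associated courses. Formula 5 multiplies the count of reported courses by the ratio of all diarrhea-associated courses to linked ones, the same multiplier as in metrics 1 to 4. All metrics are compared between scenarios as a relative and as an absolute difference.

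**The concern.** A course given for something other than diarrhea has no row in a file of diarrheal episodes, and neither does a bystander exposure during such a course. The named dataset therefore cannot supply the counts that metrics 5 and 7 call for, and no sentence says how those counts enter the simulation.

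The gap matters for the relative difference. A vaccine that removes only diarrheal courses must show a smaller percent effect on all courses than on diarrheal courses. If the non-diarrhea courses are missing from the base, that dilution is lost. Formula 5 adds a second difficulty: once the missing courses are put in, its multiplier applies to them although it describes linkage of diarrheal courses only.

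**Working it through.** The Protocol gives no course counts or expected reductions, so it has no figure to reproduce. The check is algebra on the printed formulas, with assumed inputs.

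**Notation**
- D: linked, antibiotic-treated diarrheal courses in the episode file.
- r: all diarrhea-associated courses divided by linked ones (the multiplier in formulas 1 to 5).
- s: diarrhea share of all courses, so all courses T = rD/s. Assumed 0.2 to 0.7.
- f: fraction of D prevented. Assumed 10% for illustration; it cancels from the overstatement factors.
- k: exposures per non-diarrhea course relative to a diarrheal course. Assumed 0.5 to 1.5.

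Child-years are the same in both scenarios and are omitted. Only a course linked to an episode is taken to be classifiable as prevented.

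**Metric 5, episode file only.** No vaccine: rD. Vaccine: r(1 − f)D. Relative reduction = f, the same as metric 4. Absolute reduction = rfD.

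**Metric 5, non-diarrhea courses included unchanged.** No vaccine: T = rD/s. Vaccine: T − rfD. Relative reduction = rfD/(rD/s) = f × s. Absolute reduction = rfD, as before, because the unchanged courses cancel. The overstatement in the file-only relative figure is f/(fs) = 1/s.

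| s (assumed) | File only | All courses in base | Overstatement |
|---|---|---|---|
| 0.2 | 10% | 2.0% | 5.0 |
| 0.35 | 10% | 3.5% | 2.9 |
| 0.5 | 10% | 5.0% | 2.0 |
| 0.7 | 10% | 7.0% | 1.4 |

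**Metric 5, all reported courses counted, formula as printed.** No vaccine: r × T. Vaccine: r × (T − fD). Relative reduction = fD/T = f × s/r. The level is inflated by r, and the relative reduction is 1/r of its correct value. With f = 10% and s = 0.35 the correct value is 3.5%. The printed formula gives 10% × 0.35/1.25 = 2.8% at r = 1.25 and 10% × 0.35/1.5 = 2.3% at r = 1.5. The absolute reduction is still rfD.

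If the count held only linked diarrheal courses plus non-diarrhea courses, the direction is the same. With D = 1,000, r = 1.25 and s = 0.35, T = 1,250/0.35 = 3,571, non-diarrhea courses are 3,571 − 1,250 = 2,321, and the relative reduction is 100/(1,000 + 2,321) = 3.0%.

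**Metric 7, episode file only.** The diarrheal share of exposures is s/(s + (1 − s)k), so the overstatement of the relative reduction is (s + (1 − s)k)/s.
- s = 0.2, k = 1.5: (0.2 + 1.2)/0.2 = 7.0.
- s = 0.5, k = 1: (0.5 + 0.5)/0.5 = 2.0.
- s = 0.7, k = 0.5: (0.7 + 0.15)/0.7 = 1.2.

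The absolute reduction in metric 7 also depends on the two scale factors in its formula and is not assessed here.

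**The case against.** The strongest reply is that the Protocol is silent, not wrong. Metric 5 is worded as all reported courses, so counting only diarrheal rows would contradict its definition. Formula 7 uses all-course totals, so such data are evidently part of the project. Nothing forbids adding non-diarrhea courses as a constant in both scenarios, and the linked Aim 1a and 1b plans or an unseen SAP may say so. This stands to the extent that the file-only reading is not the only one available. It does not settle the matter, because the constant-total route run through formula 5 as printed still gives a wrong relative reduction unless r = 1. The Protocol itself names the dataset and prints the formulas, and the two do not fit together.

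Four stronger readings are tempting, and the document does not support them:
- **That the reductions in metrics 5 and 7 are simply wrong.** Metric 5's absolute reduction is the same under every route worked here.
- **That diarrheal courses would be over-weighted by 50,000/6,677 = 7.5 times.** This requires the simulated counts to be left unscaled beside observed totals, which the Protocol does not say. Unscaled counts would equally distort the rates in metrics 1 to 4, so it is a separate question.
- **That these two metrics carry the main message.** The seven metrics are not ranked.
- **That the file must be rebuilt and resampled by child.** The gap can be closed without that.

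**Conclusion.** The point holds as a mismatch between the stated dataset, the two overall metrics and formula 5. It affects relative reductions. From the episode file alone, metric 5's percent reduction is overstated by 1/s (5.0 to 1.4 times for s from 0.2 to 0.7) and metric 7's by about 7.0 to 1.2 times over the same s with k from 0.5 to 1.5. With all courses counted under formula 5 as printed, the error runs the other way, to 1/r of the correct value when N is the full reported total.

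The direction follows from the formulas. The sizes do not come from the Protocol: s, r, f and k are all assumptions, as is the premise that only linked courses can be marked as prevented. The actual error cannot be computed until the course counts are shown.

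**What to change.** For metrics 5 and 7, state that non-diarrhea courses and the subclinical exposures during them are taken from the existing data. Add them unchanged to both the vaccine and the no-vaccine scenario, on the same scale as the simulated diarrheal counts. Rewrite the formulas in two parts, so that the diarrhea linkage ratio multiplies only the diarrhea-associated part. In the notation above, metric 5 becomes (r × simulated linked diarrheal courses + non-diarrhea courses) per 100 child-years. Report s and r with the results so that readers can see the dilution.

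Resampling may stay at episode level for this purpose. The cost is a wording change and minor data management. The percent reductions reported for metrics 5 and 7 will be smaller than those from the episode file alone.

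### The bootstrap has no step that carries the estimation error of the Aim 1a attributable fractions, so intervals for Shigella-attributed rates, absolute reductions and any-etiology reductions are too narrow

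*Protocol*

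**What the plan says.** The Summary of the protocol sets the unit of analysis: "Analyses will be performed at the level of diarrheal episode (N=6,677) from Aim 1a". It then states "We will use the attributable fractions per episode", and these are the fractions "for diarrheal pathogens that were calculated in Aim 1a where a pathogen with an" AFe above 0.5 is taken as the cause of the episode. The simulation uses "random sampling of the dataset with replacement to a sample size of 50,000", and for precision the Summary says "95% confidence intervals for all parameters will be estimated by bootstrap with 1,000 resamples".

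The first part of the Analyses section assigns at random whether each episode labelled Shigella "would have been prevented assuming 60% efficacy". It adds one check on the label: "We will conduct a sensitivity analysis where we define shigella diarrhea by any detection of shigella rather than AFe > 0.5".

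After metric 7 the protocol says that for all seven metrics "we will compare the relative and absolute differences between the vaccine and no vaccine simulations". The September 2022 addition applies the same label to episodes whether or not they were treated.

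The protocol nowhere says that the attribution model is refitted, that AFe is drawn from a sampling distribution, or that AFe is used as a probability instead of a yes/no label.

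**The concern.** AFe is itself an estimate. If the Aim 1a estimates had come out somewhat higher or lower, episodes near 0.5 would have crossed the cut in the same direction. This error is shared across episodes. It does not average out over the 6,677 episodes, the 1,000 resamples or the 50,000 Monte Carlo draws. A bootstrap that resamples episodes with finished labels measures only how the mix of episodes varies.

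The outputs exposed to this are:

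- the Shigella-attributed rates (metrics 1, 2 and 6; September 2022 items 1 and 2);
- every absolute reduction;
- the relative reductions in any-etiology and overall metrics (metrics 3, 4, 5 and 7; September 2022 items 3 and 4).

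The last group includes the reduction in total antibiotic use, a main purpose of the project. An interval that is too tight there would overstate how well the vaccine's benefit is known.

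**Working it through.** The protocol states no interval width, so there is no figure to reproduce. The check has four steps.

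**Inputs.** From the Summary: N = 6,677 episodes, 1,000 resamples, cut at AFe > 0.5. From Analyses: 60% efficacy from 14 days after a second dose at 9 months. Not in the protocol, and therefore assumed: Shigella share p of 5% to 15%; relative standard error c of the Shigella count due to attribution error, 2% to 10%.

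**Step 1: where the label enters.** Let S be the episodes labelled Shigella, D those prevented, and T all episodes.

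- Relative reduction within Shigella: D/S. A shared shift in labelling moves D and S by nearly the same factor and cancels, provided borderline episodes resemble the rest in age.
- Relative reduction in any-etiology episodes: D/T. T does not depend on the label, so nothing cancels.
- Absolute reduction: D per child-year. Nothing cancels.
- No-vaccine value of an any-etiology metric: T per child-year. The label is not used.

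**Step 2: size for the Shigella count.** Sampling error s = sqrt((1 − p)/(N·p)). With an independent shared error c, the total is sqrt(s² + c²), and the width ratio is sqrt(s² + c²)/s. For example, p = 0.10 gives s = sqrt(0.90/667.7) = 3.67%. With c = 5% the ratio is sqrt(0.0367² + 0.05²)/0.0367 = 1.69.

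| Share p | s | c = 2% | c = 5% | c = 10% |
|---|---|---|---|---|
| 5% | 5.33% | 1.07 | 1.37 | 2.12 |
| 10% | 3.67% | 1.14 | 1.69 | 2.90 |
| 15% | 2.91% | 1.21 | 1.99 | 3.58 |

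Under a normal approximation, the coverage of a nominal 95% interval that is too narrow by a ratio r is 2Φ(1.96/r) − 1. For the 10% row this is 2Φ(1.72) − 1 = 91%, 2Φ(1.16) − 1 = 75% and 2Φ(0.68) − 1 = 50%.

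**Step 3: smaller subsets.** Metrics 1 and 2 count antibiotic-treated episodes, and metric 1 only severe ones. With s = 1/sqrt(n), an assumed n = 100 gives sqrt(0.01 + 0.0025)/0.1 = 1.12 for c = 5% and sqrt(0.01 + 0.01)/0.1 = 1.41 for c = 10%. An assumed n = 50 gives 1.06 and 1.22. The smaller the subset, the more sampling error dominates.

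**Step 4: simulated bootstrap.** This used 6,677 episodes, assumed pathogen quantities and ages, AFe = 1 − 1/OR (so AFe > 0.5 means OR > 2), an attributed share of 9.6%, 60% prevention from 9 months plus 14 days, and 1,000 resamples. The coefficient linking quantity to diarrhea was either held fixed or redrawn in each resample with an assumed coefficient of variation (CV). Widths of the 95% intervals, in percentage points:

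| Output | Fixed | CV 5% | CV 10% | CV 20% |
|---|---|---|---|---|
| Shigella share of episodes | 1.48 | 2.04 (ratio 1.37) | 3.22 (2.17) | 5.63 (3.80) |
| Reduction in any-etiology episodes | 0.99 | 1.27 (1.29) | 1.80 (1.82) | 2.91 (2.94) |
| Relative reduction within Shigella | 7.57 | 7.62 (1.01) | 7.66 (1.01) | 7.58 (1.00) |

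The simulation agrees with Step 1: the within-Shigella ratio is untouched and the other two outputs are not.

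**The case against.** Four arguments weigh against the concern.

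- **The protocol does not say that AFe is held fixed.** The bootstrap sentence gives neither the resampling unit nor what is re-estimated, and a separate analysis plan or the Aim 1a documents might. This stands as a limit on certainty. But the protocol itself prescribes the interval method and takes AFe over as already calculated, so fixed labels are the natural reading.
- **The any-detection sensitivity analysis already probes the label.** It does test dependence on the definition and deserves credit. It changes the point estimate by replacing the rule, and leaves the primary intervals as they were.
- **The size rests on assumptions.** This stands. If few episodes lie near 0.5, or AFe is precise, the ratio may be close to 1.1 or below. The 6,677 episodes also come from 1,715 children. With positive clustering and resampling by child, the sampling error is larger and the ratio smaller.
- **This is a scenario exercise with an assumed efficacy.** Intervals conditional on stated inputs are legitimate if labelled so. The protocol instead announces 95% intervals for all parameters, with no such label.

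A reader might go further and infer that every interval in the analysis will cover less than 95%. The documents do not support that. Relative reductions within Shigella-specific metrics have the label in both numerator and denominator, and the no-vaccine values of the any-etiology metrics do not use it.

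**Conclusion.** The concern holds for a defined set of outputs. If the protocol is followed as written, the 95% intervals are too narrow for Shigella-attributed rates, for absolute reductions, and for relative reductions in the any-etiology and overall metrics.

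The direction rests on fixed labels being the intended method, and on attribution error being not strongly offset by sampling error from the same children. The size cannot be computed from the protocol. Under the assumptions shown, the full Shigella count needs an interval about 1.1 to 3.6 times wider, and the any-etiology reduction one about 1.3 to 2.9 times wider in the simulation. Treated or severe subsets need less. These are illustrations, not estimates for this dataset. The change is worth making before analysis because it alters the stated precision of the overall antibiotic-use results.

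**What to change.** Within each bootstrap resample, preferably of children:

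1. refit the Aim 1a attribution model or, as an approximation, redraw its estimates from their sampling distribution;
2. recompute AFe for the resampled episodes;
3. reapply the 0.5 rule;
4. simulate prevention and compute the metrics.

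Refitting is the better choice where feasible. The Summary indicates that the earlier aims used the same children, and an independent redraw ignores the dependence this creates. The Aim 1a model is not described in the protocol, so whether a redraw is practical depends on what that model provides.

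If neither is done, state that AFe is held fixed and label the intervals as conditional on the Aim 1a attribution. Keep the any-detection analysis as a separate check on the definition.

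The full fix costs modest extra computing, no new data, and wider intervals for the affected outputs. The labelling alternative costs one sentence.
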